### 6.3 Randomisation and Blinding

*Randomisation:*

Subjects will be sequentially randomly allocated to the various intervention arms based on their allocated treatment sequence (see table 5.1). Due to the fact that there are three intervention arms, six possible treatment sequences exist . Allocation to treatment sequence will be performed by an independent investigator employed at Wageningen University, who is not involved in the study. To maintain confidentiality, this investigator will be provided with an identification number for each participant and will not come into contact with the participants. At the start of each intervention period, another researcher will provide the participants with the materials needed for their allocated intervention. This researcher will not be involved in the collection of anthropometrical, physiological or biochemical data.

Table 5.1. Possible treatment sequences for the FLAVO-study.

| Treatment sequence |             |             |             |
|--------------------|-------------|-------------|-------------|
| 1                  | Placebo     | Epicatechin | Quercetin   |
| 2                  | Placebo     | Quercetin   | Epicatechin |
| 3                  | Epicatechin | Placebo     | Quercetin   |
| 4                  | Epicatechin | Quercetin   | Placebo     |
| 5                  | Quercetin   | Epicatechin | Placebo     |
| 6                  | Quercetin   | Placebo     | Epicatechin |

*Blinding:*

Researchers and medical staff will remain blinded towards the intervention. The company providing the capsules for the intervention (Het Gelre Apotheek, Apeldoorn) will be asked to deliver the capsules with a specific code for each treatment. The company will be asked to keep a record of the coding and will provide this code upon completion of the study. In case of serious adverse events, a subject's GP may request unblinding of the treatment.

Upon completion of the study, subjects will be asked to report the sequence of intervention groups they thought they had been allocated to. In addition, all subjects will be informed of the correct sequence of interventions they were allocated to – this will be conducted by the same researcher who provided the subjects with their materials during the intervention.

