## 8. STATISTICAL ANALYSIS

Statistical analyses will be conducted based on the intention-to-treat principle. An additional per-protocol analysis will be conducted, however, the intention-to-treat analysis will remain leading. Researchers involved in the statistical analysis will remain blinded to treatment allocation. For statistical significance, a two-tailed p-value of 0.05 will be set.

All data collected during the study will be quantitative. Continuous variables will be expressed as means  $\pm$  standard deviation while categorical variables will be expressed in frequencies. Data will be tested for normality by visual inspection of Q-Q plots and histograms.

Basic descriptive analyses (including age, gender, BMI and blood pressure) will be carried out based on subject characteristics obtained during the screening and baseline measurements.

A repeated measures analysis of variance (ANOVA) will be conducted to compare differences in intraindividual responses to the treatments. Changes from  $T_0$  to  $T_1$  will be used to determine the chronic effect of the intervention. Changes from  $T_1$  to  $T_A$  will be used to determine the acute effects of the intervention. Additional paired t-tests will be carried out to compare baseline values ( $T_0$ ) of outcome measures.

For data that are not normally distributed, a nonparametric Friedman's rank test will be conducted. All statistical analyses will be carried out using the SPSS 19.0 or SAS 9.2 software packages.

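### Section 8 sends any outcome that looks non-normal, FMD included, to Friedman's test, which in this three-period crossover uses completers only, has no period term and gives no estimate against placebo

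*Protocol*

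**What the plan says.** Section 8 of the protocol sets out the following:

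- Principle: "Statistical analyses will be conducted based on the intention-to-treat principle". A per-protocol analysis is added, but "the intention-to-treat analysis will remain leading".
- Level: "For statistical significance, a two-tailed p-value of 0.05 will be set".
- Main method: "A repeated measures analysis of variance (ANOVA) will be conducted to compare differences in intraindividual responses to the treatments". The outcome is a change within a period. The change from T0 to T1 "will be used to determine the chronic effect of the intervention", and the change from T1 to TA serves for the acute effect.
- Check: "Data will be tested for normality by visual inspection of Q-Q plots and histograms".
- Fallback: "For data that are not normally distributed, a nonparametric Friedman's rank test will be conducted".

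The fallback covers every outcome. The section names no transformation, no period term and no comparison of a supplement with placebo. The only pairwise tests it mentions are paired t-tests of the T0 values.

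Four other places bear on this. Section 6.3 gives the design: "Due to the fact that there are three intervention arms, six possible treatment sequences exist". Section 3 defines the chronic effect as a comparison with placebo over four weeks. Section 4.4 assumes about 10% dropout in arriving at 40 subjects. Section 6.6 rules out replacing anyone who withdraws once the first intervention period has begun.

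**The concern.** The fallback changes more than the distributional assumption. Friedman's test ranks the three treatments within each subject, so it has four consequences here:

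- A subject who misses one period is left out altogether, although intention to treat is meant to lead.
- There is no place in it for a period effect, in a design where treatment order varies over six sequences.
- It asks whether the three treatments differ anywhere. A significant result could come from epicatechin against quercetin alone, and no effect size or interval against placebo comes with it.
- For FMD, the test that decides the primary result is settled by eye once the data are in.

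The secondary endpoints in Section 6.1.2 include many plasma concentrations (CRP, IL-6, IL-8, TNF-α, endothelin-1). If these turn out right-skewed, the fallback becomes their main analysis, and the question of supplement against placebo goes unanswered for them.

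**Working it through.** **1. Inputs and the plan's own figure.** Section 4.4 gives SD of response 2.7, chronic effect 1.3, multiplier 7.9 and dropout of about 10%. Then 7.9 × (2.7/1.3)² = 34.08, rounded up to the stated 35. The protocol gives no efficiency figure for Friedman's test.

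**2. Incomplete subjects.** 40 × (1 − 0.10) = 36 subjects with all periods, so about 4 are lost wholly to Friedman's test. A classical repeated measures ANOVA loses the same subjects.

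**3. Efficiency.** Against the within-subject F test, Friedman's asymptotic relative efficiency is 12σ²(∫f²)² × k/(k+1). For normal errors ∫f² = 1/(2σ√π), so the first part is 12/(4π) = 3/π = 0.955. With k = 3 the result is 0.955 × 3/4 = 9/(4π) = 0.716, a loss of 28.4%. On that scale 35 subjects count as 35 × 0.716 ≈ 25. The figure holds when errors are normal, or normal after taking logs and compared with the log-scale model. Against the untransformed ANOVA it depends on the error shape:

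| Error shape | Efficiency of Friedman |
|---|---|
| Normal | 0.72 |
| Logistic | 0.82 |
| t, 5 df | 0.93 |
| Laplace | 1.13 |
| Log-normal, σ = 0.5 | 1.18 |
| t, 3 df | 1.42 |
| Log-normal, σ = 1 | 5.5 |

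**4. Power by simulation.** These runs use n = 35, the 0.05 level and 20,000 trials. The 2.7 is read as the SD of a paired treatment difference, so the within-subject error SD is 2.7/√2 = 1.91. One arm has the effect 1.3.

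- Normal errors: Friedman 0.69, ANOVA 0.83.
- t errors with 3 df: Friedman 0.92, untransformed ANOVA 0.86.
- Log-normal data (log error SD 1, log effect 0.68 in one arm): Friedman 0.68, log-scale ANOVA 0.83.
- No effect (normal and t errors): both tests close to 0.05.

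The log-normal line treats each period as one value, whereas the protocol ranks raw changes. In a further simulation of raw T0-to-T1 changes in log-normal markers (n = 36, 4,000 trials, four illustrative variance settings), Friedman had power 0.75 to 0.76 against 0.83 to 0.84 for log-scale change. At a smaller effect it had 0.47 to 0.48 against 0.56 to 0.57. The gap is 7 to 10 percentage points, rather than about 14.

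**5. Period.** These runs use n = 36 balanced over the six sequences, the same SD, and the effect 1.3 in one arm (3,000 trials). The trends are illustrative, since the protocol gives none. They are trends in the within-period change itself; a slow drift in level would largely cancel in a change score.

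| Trend per period | Friedman | ANOVA, no period | ANOVA with period |
|---|---|---|---|
| 0 | 0.71 | 0.84 | 0.84 |
| 1 FMD point | 0.59 | 0.75 | 0.85 |
| 2 FMD points | 0.23 | 0.44 | 0.84 |

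With no effect and a trend of 2, the rejection rates are 0.002, 0.001 and 0.044. Leaving period out makes both simple tests conservative; it does not inflate false positives.

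**6. Can the planned outcome be logged?** Not as a change. With mean 1.3 and SD 2.7, the share of changes at or below zero is Φ(−1.3/2.7) = 0.32, and 0.50 with no effect. The log has to be taken of the T0, T1 and TA values before any differencing, and it suits positive biomarkers rather than FMD.

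**The case against.** The best defence is that the fallback applies only to non-normal data, where rank tests often do well. That is right as far as it goes. A reader might infer that Friedman's test always throws away 28% of the information, and the figures do not support this: against the protocol's own untransformed ANOVA it gains under Laplace, t with 3 df and clearly skewed log-normal errors. The 28% stands only against a log-scale analysis of roughly log-normal data.

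A reader might also infer that logging within the stated main model would cure everything. It would not. That model is specified without a period term or placebo contrasts, its classical form also drops incomplete subjects, and its change scores cannot be logged.

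Three further replies carry weight. Transformations, follow-up tests and residual checks often belong in a statistical analysis plan, which is not at hand, and Section 8 does not forbid them. The analysts are blinded to allocation, which limits the discretion that a visual check leaves. The protocol reports no distributions, so how often the fallback would be used is unknown; skewed levels need not give skewed within-subject changes, and nothing suggests that FMD itself would trigger it.

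Against this, Section 8 is not silent. It names Friedman's test as the replacement analysis, and the completers-only, no-period and no-estimate properties belong to that test whatever the error shape.

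**Conclusion.** The point holds in a limited form and should be acted on. For any outcome judged non-normal, the stated method gives a completers-only omnibus p-value without period adjustment and without an effect against placebo. That sits badly with the intention-to-treat principle in Section 8 and the placebo comparison in Section 3. About 4 of 40 subjects are affected at the assumed dropout. The conclusion does not rest on the efficiency figure.

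The efficiency loss is about 28% if a marker is roughly log-normal and the alternative is a log-scale analysis. In the simulations of raw changes it amounted to 7 to 10 points of power. It should not be quoted without those conditions. The size of any period loss depends on a trend that the protocol does not give. The test remains valid under the null hypothesis, so this concerns the question answered, the subjects used and precision, not false positives. The stated ANOVA needs the same repair on period and placebo contrasts.

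**What to change.** Replace the main-method and fallback sentences in Section 8 with wording to this effect:

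- **FMD:** a linear mixed model on its own scale, with treatment and period as fixed effects, T0 as covariate and subject as random effect. Report the epicatechin-placebo and quercetin-placebo contrasts with intervals. This choice does not depend on the look of the data.
- **Positive, skewed biomarkers:** log-transform the T0, T1 and, for acute effects, TA values before modelling or differencing. Fit the same model and report ratios of geometric means with intervals.
- **Acute effects:** the same model for TA with T1 as the baseline, following the definition in Section 8.
- **Checks:** judge fit on residuals and keep Friedman's test as a sensitivity analysis only.

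The mixed model keeps subjects who complete some but not all periods, on the assumption that data are missing at random; someone with no post-baseline value still adds nothing. No visit, sample or added subject is needed, and the packages named in Section 8 can fit the model. The one small downside is that effects on skewed markers are reported as ratios rather than in raw units. The wording should be settled before unblinding.

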## 9. ETHICAL CONSIDERATIONS

### 9.1 Regulation statement

This study will be conducted according to the Declaration of Helsinki – Ethical Principles for Medical Research Involving Human Subjects (updated October, 2008) and in accordance with the Medical Research Involving Human Subjects Act (WMO) and local regulations.

### 9.2 Recruitment and consent

Eligible participants will be recruited from the area of Wageningen and the nearby surroundings. Advertisements will be released 2 months prior to the start of the study, in which the general scope and criteria for the study will be mentioned. These advertisements will be released digitally (via email) , by posters and by mail. In addition, participants from a recent similar study (the KaNa-trial) will be asked upon completion of the study, whether they would be interested in taking part in this study. Participants who have completed other nutritional intervention studies at Wageningen University will also be approached.

Subjects who express an interest in taking part will be sent an information brochure explaining the aim and design of the study as well as the inclusion/exclusion criteria required in order to take part. Subjects who are still interested in taking part in the study after having read the information brochure will be provided with contact details in order to arrange an appointment for an information session. Those who do not contact the research team within 2 weeks of receiving the information brochure will be contacted by telephone to see whether they are still interested in taking part in the study.

During the information session, potential participants will be given an initial informed consent form for the information session and screening. Standard SBP and DBP measurements will be taken for all participants who attend the information session. After the information session, potential participants will be given a short medical history and lifestyle questionnaire which they can complete at home. Subjects who meet the criteria based on the health and lifestyle questionnaire, BP measurements and who return a signed informed consent form will be invited to a screening session at the university. This screening session will take place no earlier than 4 weeks before the start of the study. Upon completion of the screening session, those who meet the inclusion criteria and are still interested in taking part will be invited to take part in the study.

### 9.3 Benefits and risks assessment, group relatedness

The risks for participation in this study are low. For all supplements used, a safety report has been obtained (see Appendix II). A potential burden for the subjects may be the restricted diet (i.e. chocolate, tea, red wine, apples and onions). In addition, subjects will be required to attend 6 assessment sessions (including FMD and BP measurements) following an overnight fast, which could be considered as an additional burden.

### 9.4 Compensation for injury

The sponsor/investigator has a liability insurance which is in accordance with article 7, subsection 6 of the WMO.

The sponsor (also) has an insurance which is in accordance with the legal requirements in the Netherlands (Article 7 WMO and the Measure regarding Compulsory Insurance for Clinical Research in Humans of 23th June 2003). This insurance provides cover for damage to research subjects through injury or death caused by the study.

1. € 450.000,-- (i.e. four hundred and fifty thousand Euro) for death or injury for each subject who participates in the Research;
2. € 3.500.000,-- (i.e. three million five hundred thousand Euro) for death or injury for all subjects who participate in the Research;
3. € 5.000.000,-- (i.e. five million Euro) for the total damage incurred by the organisation for all damage disclosed by scientific research for the Sponsor as 'verrichter' in the meaning of said Act in each year of insurance coverage.

The insurance applies to the damage that becomes apparent during the study or within 4 years after the end of the study.

### 9.5 Incentives

Subjects who complete the main study (part 1) will receive €250. Subjects who fail to complete the study will be compensated based on the amount of (assessment) days completed. Subjects who complete the additional cocoa study (part 2) will receive an additional €50. The amount of compensation provided will be calculated based on the measurements taken during each assessment day according to pre-determined rates specified by the Division of Human Nutrition at Wageningen University. These rates are based on the degree of burden and length of duration of the measurement. In addition,

participants will receive compensation for travel costs based on the estimated distance travelled.

## **10. ADMINISTRATIVE ASPECTS AND PUBLICATION**

### **10.1 Handling and storage of data and documents**

Each participant will be provided with a randomly-assigned individual identification code. To ensure confidentiality, only the researchers involved in the study will have access to the identity codes. During statistical analyses, all values will be coded by the identification code, thereby ensuring anonymity.

All data will be stored digitally on the internal network of the Division of Human Nutrition at Wageningen University. This internal network will remain password-protected and the password will only be made available to the investigators, research assistants and potential graduate students involved in the study after completion of a confidentiality agreement.

Hard copies (e.g. completed questionnaires and reports of physiological measurements) will be kept for a duration of 24 months after completion of the study, after which all copies will be destroyed. Blood samples will be stored in a locked freezer at Wageningen University and will be coded by the identification code. This study will be registered at the *College Bescherming Persoonsgegevens* (College Protection Personal Information).

### **10.2 Amendments**

Amendments are changes made to the research after a favourable opinion by the accredited METC has been given. All amendments will be notified to the METC that gave a favourable opinion.

### **10.3 End of study report**

The investigator will notify the accredited METC of the end of the study within a period of 8 weeks. The end of the study is defined as the last patient's last visit. In case the study is ended prematurely, the investigator will notify the accredited METC - including the reasons for the premature termination.

Within one year after the end of the study, the investigator/sponsor will submit a final study report with the results of the study, including any publications/abstracts of the study, to the accredited METC.

#### **10.4 Public disclosure and publication policy**

The results of this study will be submitted for publication in international scientific journals and will constitute a part of [name]'s final PhD dissertation. In addition, the sponsor is entitled to review and provide comments on manuscripts and/or articles prior to publication.

The sponsor may delay publication for up to three months after analysing the research results if it is applying for a patent or for other important reasons. Participants can receive a summary of the results with averages of the group after the end of the study. Finally, the trial itself will be registered at ClinicalTrials.gov and will be allocated a specific trial registration number.

## Appendix I: List of Flavonoid-Rich Foods and Diet Restrictions

Tijdens de studie wordt u gevraagd om bepaalde voedselproducten die een hoge concentratie aan flavonoïden bevatten te vermijden. Als u veel van deze producten consumeert, zal uw flavonoïdeninname stijgen waardoor het moeilijk wordt om een onderscheid te maken tussen de effecten van de supplementen en de effecten van de flavonoïden uit uw dieet.

Producten die een hoge concentratie aan flavonoïden bevatten zijn **thee, cacao, chocola, appels, uien** en **rode wijn**. Dit zijn de producten waar u rekening mee moet houden tijdens de FLAVO-studie. Graag willen wij u vragen om (zo ver als mogelijk is) deze producten te vermijden. Thee hoeft u niet helemaal te vermijden, hier mag u **één kop per dag** van drinken.

Vóór het begin van de studie zult u een dagboek ontvangen waarin u bepaalde gebeurtenissen kunt vermelden worden. Mocht het gebeuren dat u per ongeluk meer dan één kop thee of (bijvoorbeeld) een appel eet, kan dit in het studie dagboek genoteerd worden.

Tijdens de gehele studie geldt het volgende dieetadvies:

1. Niet meer dan één kop **thee** per dag drinken.
2. Geen **appels** (of appelproducten zoals appelsap, appelgebak, appelmoes) eten/drinken.
3. Geen puur/melk **chocola** eten (of cacaoproducten zoals chocoladetaart, koeken, chocolademelk..). Witte chocolade mag wel gegeten worden.
4. Geen **uiensoep** eten. **Andere gerechten waarin uien verwerkt worden (zoals hutspot en hachee) kunnen gerust gegeten worden.**
5. Niet meer dan 1 glas **rode wijn** per dag drinken. Witte wijn, rosé wijn en port mag wel gedronken worden.

Mocht u twijfelen of vragen hebben, dan kunt u contact met ons opnemen door op werkdagen te bellen naar [name] of te emailen naar [[contact]](mailto:[contact])

[figure not shown][figure not shown][figure not shown][figure not shown][figure not shown]

## **Appendix II: Supplement Safety Reports**
